### Timeline

Enrolment is estimated to be completed within a period of 20 months.

### Patient and public involvement

Two patient representatives, who are currently or have previously undergone cancer treatment themselves, will be involved as co-researchers in scoring the observer-perceived measure OPTION5 to investigate if patients identify elements of perceived significance in the consultations not noticed by the researchers. The rating team consisting of two researchers and two patient representatives will initially meet for training in scoring to ensure that they are calibrated in scoring the five themes of OPTION5. The 70 audio recordings will be divided between the two patient representatives, while the two researchers listen to and score all 70 audio recordings.

The process and the patients' influence on the analysis process will be documented in an impact log [33]. The log is completed with the patients, and the day's audio recordings are evaluated and debriefed. The entire process of involvement will be reported and documented using GRIPP2 [34]. The patient representatives will also be asked to complete the PPEET self-reported co-researcher questionnaire [35].

### Statistical methods

Data will be stored in a secure server in OPEN Analyse. Descriptive analyses will be performed to explore exchangeability between the two study arms. Data will be presented in a table describing the study population on key characteristics.

The main analyses will be performed as mixed effect models by incorporating the clinician as a random effect. If there is no significant variation, analyses will be performed using linear regression. The 95% confidence intervals will be estimated using bootstrapping. In case of a screwed distribution on key characteristics (non-exchangeability) between the study arms, multivariate analyses will be performed adjusting for potential confounding factors.

Primary and secondary outcomes will be analysed as sum scores and sub scores, and sub-analyses including stratification by sex and age groups. Continuous measures will be presented as mean with standard deviations (SD) or median with interquartile range (IQR) depending on if the findings are normally distributed?. Means will be compared using a 2-sided t-test, medians using a non-parametric K-sample test on the equality of medians. A 2-sided *p*-value of ≤ 0.05 will be used to determine significance.

The consultation length will be measured using the audio recordings and analysed descriptively.

All analyses will be performed as intention-to-treat analyses, and in case a patient did not access the app before consultation, per-protocol analyses will be performed as a sub-analysis. Missing data will be handled according to the scoring instructions of the instruments.

Audio recordings of clinician and patient consultations will be rated by a team consisting of the principal investigator, a second researcher, and two patient representatives. Before rating, an initial calibration between the raters will be performed to avoid inter-observer variation and to reach a scoring consensus. Any discrepancies will be resolved by agreement or a fifth rating. Audio recordings will be stored in a secure server at OPEN.

The team rating the audio recordings will be blinded such that raters will not know which arm the patients were randomised. Overall OPTION scores will be compared using the Wilcoxon-Mann–Whitney two-sample rank-sum test. Inter-rater reliability will be calculated using Interclass Correlation Coefficients (ICC). A reasonable threshold is above 0.6 [36].

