### Sample size

According to the SDM Process_4 user guide, Sepucha and Fowler [24] suggest assumptions for the sample size calculations, including a common standard deviation of σ = 1 and a mean difference between intervention arm I and II at δ = 0.5*SD. Further, assuming a significance level of α = 0.05 and a statistical power of 1-β = 0.8 (80%), a total of 204 patients will be recruited in the study which included an extra 10% to compensate for missing data and dropouts.

For secondary outcomes, the observer-perceived patient involvement in SDM (OPTION5) will be used to analyze the audio recordings of the consultations between patient and clinician. A separate sample size calculation was conducted for this outcome; based on a previous RCT study with a mean OPTION5 score of 26.6 in the control arm [31], the calculation of sample size for the OPTION5 measure requires 35 patients in each arm to achieve 80% power (alpha at 0.05) to demonstrate a difference of at least 13.4 points (50% increase in observed level of SDM) [31]. Patients will be consecutively asked for permission to audio record the consultation until the required sample size is achieved; hence, no dropouts or missing data are expected. Therefore, a total of 70 audio recordings are required.

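### Age-stratified results, if read against p ≤ 0.05, cannot show whether the effect differs by age; an exploratory arm-by-age interaction is a cheap improvement

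*Protocol article*

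**What the plan says.** The protocol article, Statistical methods, says that primary and secondary outcomes will be analysed as total and component scores, with "sub-analyses including stratification by sex and age groups". The tests follow in the same paragraph: "Means will be compared using a 2-sided t-test", with a test on medians as the alternative, and a two-sided p "value of ≤ 0.05 will be used to determine significance".

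The paragraph names no arm-by-subgroup interaction and gives no age cut points. It does not call the stratified results descriptive or exploratory, whereas the next paragraph says explicitly that consultation length is only described.

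Elsewhere, the Sample size section covers only the overall comparison of arms for the primary outcome. The Eligibility criteria do not restrict sex, and the randomisation is described as blocked, without stratification by sex or age.

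**The concern.** A significant result in one stratum beside a non-significant result in another is not evidence that the effects differ. Each stratum has fewer patients and lower power than the whole trial, so an effect that is the same at every age can easily pass the threshold in one group and miss it in another. Whether the effect differs is answered by estimating the difference between the stratum effects, with its uncertainty.

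Age is the factor where this could matter. The trial compares a digital aid with a paper one, and the Introduction notes that digital health does not suit every patient. A report that one age group gains from a format and another does not would be easy to draw from stratified p-values, and could influence how the aid is offered.

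The sex split raises a smaller point. In a breast cancer sample the stratum of men is likely to be too small for a within-stratum test to be informative.

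**Working it through.** **Inputs.** From Sample size: "a common standard deviation of σ = 1", a difference of 0.5 SD, "assuming a significance level of α = 0.05", 80% power, and "a total of 204 patients will be recruited in the study", which includes 10% for missing data and dropout. From Study design: 1:1 allocation. Assumed, because the article does not give them: the number and size of the age groups, and the share of men.

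**The plan's own figure.** n per arm = 2(1.960 + 0.842)² / 0.5² = 62.8, so 63 per arm and 126 in total (64 and 128 with the t distribution). Adding 10% gives 139–143, depending on the method. The stated inputs therefore do not reproduce 204. That is a separate matter; here 204 is taken as given. With 10% lost, 204 × 0.9 = 183.6, about 184 analysed, and overall power at 0.5 SD is about 92%.

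**Separate tests in age strata, true effect 0.5 SD in every stratum.** Power per stratum comes from the noncentral t distribution, with noncentrality 0.5 / √(2/n) for n per arm within the stratum.

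- Two equal groups, n = 184/4 = 46: noncentrality 2.40, power 0.660. Exactly one significant: 2 × 0.660 × 0.340 = 0.449.
- Three equal groups, n = 184/6, about 31: noncentrality 1.97, power 0.491. Neither all nor none significant: 1 − 0.491³ − 0.509³ = 0.750.

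A simulation of the two-group case gave 44.7%.

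**Sensitivity of the share of trials with mixed results.**

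| Age groups | 184 analysed | 204 analysed |
|---|---|---|
| two equal | 45% | 42% |
| one third / two thirds | 51% | 48% |
| three equal | 75% | 75% |
| four equal | 83% | 85% |

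**Interaction test, two equal groups.** The difference between two stratum effects rests on four cells of N/4 patients, each with SD 1, so SE = √(4 / (N/4)) = √(16/N).

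- N = 184: SE = √(16/184) = 0.295. Power for a 0.5 SD difference in effect: Φ(0.5/0.295 − 1.96) = 0.40. Difference detectable with 80% power: 2.80 × 0.295 = 0.83 SD.
- N = 204: SE = 0.280, power 0.43, detectable difference 0.78 SD.
- If the effects are equal, the test signals a difference in 5% of trials by construction.

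**Men.** Expected number among 204: 0.5% gives 1.0, 1% gives 2.0, 2% gives 4.1, 5% gives 10.2. At 1%, the chance of no men at all is 0.99²⁰⁴ = 0.13. Even five men per arm would give only about 11% power for 0.5 SD.

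**The case against.** The strongest objection is that the article never says stratum p-values will be compared. The 0.05 threshold is a convention for the whole section and does not mention strata. The aims, hypothesis and outcomes pose no question about effect modification, and the stratified work is already ranked as sub-analysis. Cut points, an interaction term and an exploratory label are often left to an analysis plan, and one not shown here could contain them. The main analyses are to be model-based with bootstrapped 95% CIs, which could also be applied to the strata.

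Much of this stands. A reader might infer that the trial intends to declare age-specific effects from stratum p-values, and that 45% or 75% of such trials would make a false subgroup claim. The text does not support that: the percentages are rates of mixed results, and become claims only if someone draws the inference. Nor is the absence of cut points or of an interaction term an error in itself.

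What remains is that the article does name a method for the subgroups, stratification, and puts tests and a significance rule beside it with nothing to limit how the strata are read. That method does not estimate a difference in effect, so the point is not merely a request for missing detail.

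A reader might also infer that the sex split would mislead. Nothing in the documents shows this. The share of men is an assumption, and a test in so few men would be visibly uninformative or impossible to compute.

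**Conclusion.** The point holds in a limited form. Stratified results read against 0.05 cannot show whether the effect differs by age. With 184 analysed and 0.5 SD at all ages, mixed results would arise in about 45% of trials with two equal age groups and about 75% with three.

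These figures assume plain t-tests, equal-sized groups and exactly the planned effect in each. Under the other splits and the full 204 patients examined, the share stays between 42% and 85%, so the conclusion does not depend on one choice. The point about men rests on an assumed share of 0.5–5%.

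The primary comparison and its conclusion are not affected. This is a cheap improvement of low severity.

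**What to change.** - Estimate effect modification by age with an arm-by-age interaction term in the main model. Age may be continuous or grouped by cut points fixed in advance; continuous age assumes a linear trend unless that is relaxed. Report the term with its 95% CI and label it exploratory.
- Show age-stratum estimates with CIs and without stratum p-values.
- Report men descriptively instead of testing within sex.

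The cost is a change of wording and one model term, with no new data or patients. The downside is low power: about 40% for a 0.5 SD difference between two equal groups at N = 184. The interaction will seldom settle whether the effect differs, and a non-significant result must not be read as proof that the effect is the same at all ages.

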### Outcomes

The primary outcome is the extent to which patients are involved in a shared decision making process reported by the patient using the SDM Process_4 questionnaire [24]. This instrument has four items and demonstrated good acceptability with high response rates and very low missing data. In a national study of 10 different medical conditions, the SDM Process_4 did not show floor or ceiling effects. Calculations showed moderate to good reliability (ranging from 0.54 to 0.87), and retest reliability was moderate (0.64). The construct validity assessment indicated that higher scores correlated with better decision quality and that patients were less likely to think they had made the wrong decision [24].

Secondary outcomes, using well tested instruments, are the patient-perceived level of SDM [25], patient engagement [26], preparation for decision making scale [12], decisional conflict scale [7], and Control preferences Scale [27]. Additional secondary outcomes are consultation length, clinician-perceived level of SDM [28], and observer-perceived patient involvement in SDM [29, 30]. All questionnaires are validated and translated into Danish (see Table 1 for further details). Patients’ demographic characteristics will include age, gender, education, occupation, and living arrangements.

**Table 1 Tab1:** Content of data collection outcome measures

Distribution	Measurement instrument	Description	Item no., range and scoring
Patient Q1	Decisional Conflict Scale [7]	Patient-reported perceived measure of four of five dimensions of decisional conflict (e.g., uncertainty, uninformed, unclear values, unsupported)	12 items 5 point Likert scale (0–4) Mean standardized score*25 (0–100)
	Control Preference Scale [27]	Patient-reported preference for the patient’s preferred role in shared decision making	1 item with five statements (pick one)
	Access to digital PtDA	Patients in intervention arm II are asked if they have accessed and used the digital PtDA	Yes/No – if no, to state the reason: • Cannot install the app • Cannot open the PtDA in the app • Problems with e-Boks • Other technical issues • Did not have the time • Do not want to see the options • Other cause / do not know
Patient Q2	Shared Decision Making Process 4 (SDM Process_4) [24]	Patient-reported engagement	4 items 4 point Likert scale (0–1, yes/no) Points are summed (0–4)

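### The primary outcome has two unranked routes to a p-value, and one of them can end in a median test that does not address the mean difference the trial was sized on

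*Protocol article*

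**What the plan says.** The Statistical methods section of the protocol article describes the inference in two consecutive paragraphs.

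- **Model route.** "The main analyses will be performed as mixed effect models by incorporating the clinician as a random effect". This has a fallback: "If there is no significant variation, analyses will be performed using linear regression". Confidence intervals are to be bootstrapped.
- **Test route.** The next paragraph opens by naming primary and secondary outcomes together. Continuous measures are shown as mean with SD or median with IQR, "depending on if the findings are normally distributed". It continues: "Means will be compared using a 2-sided t-test, medians using a non-parametric K-sample test on the equality of medians". It closes with the two-sided 5% threshold for significance.

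Table 1 (Outcomes) describes the primary score as four items, with "Points are summed (0–4" as the scoring. The Sample size section assumes "a common standard deviation of σ = 1" and "a mean difference between intervention arm I and II at δ = 0.5*SD", so the design rests on a difference in means.

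**The concern.** One outcome can yield a p-value from a mixed model, a linear regression, a t-test or a median test. The text does not rank the model route against the test route. The section calls the models the main analyses, yet the significance threshold stands beside the t-test and median test. If the routes disagree, the document does not say which one settles the trial.

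The median branch raises two further problems. It concerns a different quantity from the one in the sample size calculation. It also reduces each patient's score to above or not above the pooled median, which discards information and handles ties poorly on a short discrete scale. At stake are power, a stable estimand, and the ability to show that the choice of test did not follow the result.

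**Working it through.** **Inputs from the protocol.** σ = 1, δ = 0.5, two-sided α = 0.05, power 80%, total 204 including 10% extra, 1:1 allocation, score range 0–4.

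**The plan's own figure.** n per arm = 2(1.96 + 0.84)²/0.5² = 62.8, so 63 per arm and 126 in total. With 10% extra this is 139 (126 × 1.1) or 140 (126/0.9). The stated 204 is not reproduced. That is a separate point, and 204 is taken as given here. Less 10%, it leaves 204 × 0.9 = 183.6, about 92 per arm.

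**Normal-theory power.** For the mean comparison, power ≈ Φ(0.5·√(n/2) − 1.96). The median test has asymptotic relative efficiency 2/π = 0.637 under normality, so the first term is multiplied by √0.637 = 0.798.

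| n per arm | Mean comparison | Median test | Loss (points) |
|---|---|---|---|
| 63 | Φ(2.806 − 1.96) = 80.1% | Φ(2.239 − 1.96) = 61.0% | 19 |
| 92 | Φ(3.391 − 1.96) = 92.4% | Φ(2.706 − 1.96) = 77.2% | 15 |
| 102 | Φ(3.571 − 1.96) = 94.6% | Φ(2.849 − 1.96) = 81.3% | 13 |

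**Simulation on discrete scores.** Table 1 does not fix the step size of the score, so it was assumed. Normal scores were rounded and clipped to 0–4, with SD about 1 and a true difference of about 0.5.

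- At 92 per arm the t-test had about 88–92% power and the median test 68–79%. The two verdicts differed in 14–24% of trials.
- With steps of 1, 1/2, 1/3 and 1/6, several scale locations and 63 to 102 per arm, the loss ran from about 10 to 24 points, mostly 13–19.

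**How often the normality switch would trigger.** The protocol names no rule, so several were tried with a true difference present.

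| Rule | Trigger rate |
|---|---|
| Shapiro-Wilk at 5%, steps of 1 or 1/2 | 99–100% |
| Shapiro-Wilk at 5%, steps of 1/3 | 81–100% |
| Shapiro-Wilk at 5%, steps of 1/6 | 56–100% |
| D'Agostino at 5%, mid-scale scores | about 14–41% |
| D'Agostino at 5%, scores near the ceiling | about 52–84% |
| Absolute skewness above 1 | 0–4% |

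**Type I error at 92 per arm.** A switch on Shapiro-Wilk, fixed in advance, gave 3.7–5.1%. Counting a trial as positive if either the t-test or the median test was significant gave 6.9–7.9%.

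**The case against.** The strongest reply is that the section does name a main analysis, the mixed model. The t-test and median sentence directly follows the one on presenting means or medians, so it can be read as accompanying the descriptive tables. The ranking of tests and the normality criterion could also sit in an analysis plan that is not shown. The ambiguity is real, so the power loss has to be stated as conditional on the median test deciding. The reply does not remove the point. The paragraph names the primary outcome, says that the summaries are compared, and carries the significance threshold. These are stated rules that compete, not details left for later.

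Four stronger readings are tempting and are not supported:

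- **That the median test will almost always be used.** This holds only for a Shapiro-Wilk type rule on coarse scores. Under a skewness rule it would seldom be used.
- **That the trial would be badly underpowered.** By normal theory the median test keeps 77–81% power at 92–102 per arm, close to the planned 80%, because 204 exceeds what the stated inputs need. In discrete simulation it falls to about 65–84%. The loss is relative to the mean comparison at the same n.
- **That the switch inflates the error rate.** It does so only if either result may be reported, which the text neither says nor rules out.
- **That the test of clinician variance damages the result.** With 10 clinicians and an ICC of 0.05 (both assumed), the variance would be significant in about 46% of trials, so the switch would be frequent. Patients are individually randomised, however, and both models target the same mean difference. With an ICC of 0.05–0.10, analyses with and without clinician (as fixed effects) gave type I error of 4.6–5.0% and 4.8%. Power was 92–94% and 92–93%, and verdicts differed in only 3–4% of trials. This assumes no arm-by-clinician interaction.

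**Conclusion.** The point holds in a conditional form and should be fixed. The primary outcome has two inferential routes with no stated hierarchy, and one of them depends on a normality check with no criterion. If the median test decides, the trial no longer tests the mean difference it was sized on. It then gives up about 15 points of power at 92 per arm by normal theory, or roughly 10–24 points across the simulated settings.

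These sizes rest on the protocol's SD of 1 and difference of 0.5, and on assumed score granularity and location. Since the trigger rate runs from near 0% to near 100% with the rule chosen, the branch taken would depend on a choice the protocol leaves open. That is the reason to settle it before analysis.

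**What to change.** State one primary analysis: the difference between arms in mean SDM Process_4 sum score, from a linear mixed model with arm as fixed effect and a clinician random intercept. Keep the intercept whether or not its variance is significant, and take both the p-value and the 95% interval from that same model. If bootstrapping is kept, it should be of that model's arm effect.

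For the primary outcome, delete the normality-driven choice between t-test and median test as an inferential step. Show median and IQR descriptively where useful, and label any rank-sum or median test as sensitivity only.

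The cost is a few sentences in the Statistical methods section, with no added patients or data. A mean comparison on a bounded score at about 92 per arm does not need the normality safeguard: the simulated t-test kept type I error at or just below 5%.

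The change should be dated before the data are analysed, because afterwards the choice cannot be shown to be independent of the result.

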**Fig. 1 Fig1:**
[figure not shown]
Recruitment procedure flow diagram with eligibility, interventions and data collection. Q: Questionnaire. O: Observer measure. PI: Principle investigator

The principal investigator telephones the eligible patients, identified by the study nurse, to obtain oral consent and randomise them. Randomisation will be performed as block randomisation with an equal allocation ratio (1:1) using a computer-generated table of block sizes of 4 or 6, created and supervised by a data manager at OPEN, Open Patient Data Explorative Network, Odense University Hospital, Region of Southern Denmark.

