### Interventions

Intervention arm I will be introduced to a paper-based PtDA by the clinician in the consultation. Participants in intervention arm II will be invited to access the digital PtDA via an app before the consultation. The paper-based PtDA will not be used during consultation in intervention arm II. Both arms will be exposed to the same PtDA in terms of the lexical, visual and structural content, only the format (digital versus paper-based) is different.

The PtDA used in this study is based on the generic patient decision aid template developed and clinically tested by the Center for Shared Decision Making, Vejle Hospital, Denmark and based on the International Patient Decision Aid Standards (IPDAS) [22]. The PtDA is customised for use by patients with early-stage breast cancer who went through curative surgery. The PtDA specifically indicates the decision about having none, one or more adjuvant treatments depending on the patient's value assigned to survival rates, side effects, long-term consequences, and quality of life. The PtDA involves a five-step procedure to make explicit clarification of the patient’s values for adjuvant treatment and presents options A) chemotherapy, B) radiation, C) hormone therapy, D) antibody therapy, and E) no treatment including benefits and harms of each option, outcome probabilities, and personal stories describing experiences of others that are relevant to the decision at hand. The options offered to the patient depend on the patient’s age and tumor characteristics. The paper-based version has been available for use during consultations in the clinic since 2017 [23].

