### Data collection

Study data will be collected and managed using the REDCap electronic data capture tool (copyright Vanderbilt University, version 12.0.33 [32]) hosted at OPEN (Open Patient Data Explorative Network, Odense University Hospital, Region of Southern Denmark). After oral consent, patients will be randomised via REDCap and are immediately sent an electronic questionnaire via e-Boks to be answered before the consultation (a total of 13 questions, Patient Q1 in Table 1). E-Boks is a secure national platform for digital, personal mail used by public authorities to citizens. All Danish citizens are required to use e-Boks but can be exempted from use if they fulfil specific requirements. If exempted from use, the patient will receive the questionnaire by mail. In the first questionnaire, enrolled patients give their written, electronic consent to participate and are asked to indicate if they consent to audio recording of the consultation. Patients in intervention arm II will be asked to checkmark if they have accessed and used the digital PtDA and, if not, to state the reason it was not used.

The day after the consultation with the oncologist discussing adjuvant treatment, enrolled patients will receive the second questionnaire from REDCap (a total of 42 questions, Patient Q2 in Table 1). Patients in intervention arm II will also be asked to checkmark if the clinician used the paper-based PtDA during consultation. The patient will receive a reminder to complete the questionnaire after three and six days.

Clinicians will be administered one 9-item questionnaire on paper which they are asked to fill in right after the consultation while they have the consultation fresh in mind (Clinician Q2, Table 1). Clinicians will also be asked if patients in intervention arm II unprovokedly took out their smartphone or tablet during the consultation to use the digital PtDA. Afterwards, answers will be registered manually in REDCap by the principal investigator.

Audio recordings of clinician and patient consultations (N = 70) are collected (Observer Q1, Table 1) for later analysis. The nurse participating in the consultation is responsible for initiating the recording.

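### The OPTION5 raters are described as blinded, but the principal investigator, who randomises the patients, scores every recording

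*Protocol article*

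**What the plan says.** All places are in the protocol article.

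- **Blinding claim** (Statistical methods): "The team rating the audio recordings will be blinded such that raters will not know which arm the patients were randomised".
- **Who rates** (same section, the paragraph before): the recordings are "rated by a team consisting of the principal investigator, a second researcher, and two patient representatives".
- **How much each rater scores** (Patient and public involvement): the recordings are split between the two patient representatives, "while the two researchers listen to and score all 70 audio recordings".
- **Who randomises** (Recruitment procedure, text below Fig. 1): "The principal investigator telephones the eligible patients, identified by the study nurse, to obtain oral consent and randomise them". Data collection adds that this is done in REDCap after oral consent.
- **Who enters the clinician forms** (Data collection): "Afterwards, answers will be registered manually in REDCap by the principal investigator". These forms ask whether an arm II patient took out a phone or tablet to use the digital aid (also Table 1).
- **What is heard in the consultation** (Interventions): "Intervention arm I will be introduced to a paper-based PtDA by the clinician in the consultation"; for the other arm, "The paper-based PtDA will not be used during consultation in intervention arm II".
- **Discrepancies** (Statistical methods): settled by agreement or by a fifth rating.
- **Hypothesis** (end of the Introduction): patients experience more shared decision making with the in-consult aid, which is arm I.

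**The concern.** The blinding statement covers the whole team, yet one member of that team carries out the allocation. OPTION5 is a judgement score, so a rater who knows the arm and works under a directional hypothesis can lean towards it without meaning to. That rater may also influence the final score when discrepancies are settled by agreement.

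This matters because of the role OPTION5 plays. SDM Process_4, SDM-Q-9 and CollaboRATE come from patients who know what they received, and SDM-Q-doc comes from the clinician in the room. OPTION5 is the only measure of the level of shared decision making scored from outside the consultation, and it has its own sample size calculation. A results paper that repeated the blinding sentence would invite readers to treat OPTION5 as protected from observer bias when, for one rater, the described design does not protect it.

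**Working it through.** **Does the claim hold? Reading the sections together, rater by rater**

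1. *Principal investigator.* Statistical methods lists this person and a second researcher as the non-patient raters. Patient and public involvement says the two researchers score all 70 recordings. The principal investigator therefore scores 70 of 70. The same person randomises patients (Recruitment procedure) and enters forms with an arm II item (Data collection). No section describes a step that hides the allocation from this person. The claim fails for this rater.
2. *Second researcher.* The article describes no role beyond rating. The only visible route to the allocation is the audio.
3. *Patient representatives.* As for the second researcher.
4. *Audio.* Under Interventions, the paper aid is introduced during the arm I consultation and is not used in arm II. The recording is of that consultation, so the talk will probably differ by arm. The cue is imperfect: Table 1 asks arm II patients whether they were shown the paper aid, and asks clinicians whether arm II patients took out a device, so the trial itself allows for crossover.

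**The plan's own OPTION5 figure**

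This gives a scale for the illustration below; the contradiction does not depend on it. Inputs from Sample size: 35 per arm, difference 13.4 points, 80% power, alpha 0.05 (taken as two-sided, as in Statistical methods). No SD is given, so it is solved for:

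- SD = 13.4 / [(1.960 + 0.842) × √(2/35)] = 13.4 / (2.802 × 0.239) ≈ 20.0.
- Check: n = 2 × 2.802² × 20² / 13.4² ≈ 34.98, rounded up to 35 per arm.
- With SD 15 or 25 instead, n would be 20 or 55 per arm. The stated 35 is consistent with an SD of 20; it is not shown to be wrong.

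**What a lean could do (illustration only)**

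- OPTION5 has 5 items scored 0–4, and the item mean is multiplied by 25. One point on one item is 25/5 = 5 points on the 0–100 scale.
- Each recording gets three ratings: two researchers and one patient representative. If the analysed score were their mean, which the article does not state, a one-point lean on one item by one rater, in one arm only, would move that arm by 5/3 ≈ 1.7 points, and 1.7/13.4 ≈ 12% of the target difference.
- If that rater's value were adopted every time, the move would be 5 points, and 5/13.4 ≈ 37%.
- Two-sided type I error with no true difference, 35 per arm and a systematic shift b between arms, from the noncentral t with 68 degrees of freedom and noncentrality b / (SD × √(2/35)):

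| Shift b | SD 15 | SD 20 | SD 25 |
|---|---|---|---|
| 0 | 5.0% | 5.0% | 5.0% |
| 2 | 8.5% | 7.0% | 6.3% |
| 3 | 13.1% | 9.5% | 7.9% |
| 5 | 28.0% | 17.8% | 13.1% |

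The plan compares OPTION5 by a rank-sum test, so these t-test figures are approximate.

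**The case against.** The strongest defence is that the contradiction concerns one rater and one secondary outcome, measured in 70 of 204 patients. The principal investigator may have forgotten individual allocations by the time of rating, and recordings may be coded. Discrepancies need not be settled by consensus: since the team has four members, a fifth rating suggests someone outside it. Some audible difference is unavoidable when an in-consult aid is compared with a pre-consult one.

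Much of this stands as a limit on the point, but it does not rescue the sentence. Forgetting is not blinding, the article mentions no coding, and coding would not remove audible content. Nor is this a detail left to a fuller document: the issue is what the article asserts.

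Some stronger readings that a reader might infer are not supported:

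- *That the whole team is unblinded because the audio gives the arm away.* No section says so. For the other three raters it is an inference, weakened by possible crossover.
- *That OPTION5 is the only outcome not reported by a participant.* Consultation length is also taken from the recordings. OPTION5 is the only such measure of the level of shared decision making.
- *That agreement carries the principal investigator's lean into every final score.* The fifth-rating route is an alternative.
- *That 12% or 37% estimates the bias.* Both rest on an assumed lean confined to one arm; a lean common to both arms cancels.

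**Conclusion.** The blinding statement is wrong as written for the principal investigator, and nothing else in the article repairs it. For the second researcher and the patient representatives, unblinding through the audio is likely but not documented.

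The consequence is a risk of observer bias in OPTION5, probably in favour of arm I given the stated hypothesis. The size of that bias cannot be derived from the article. The illustrated shifts and the SDs of 15 and 25 are assumptions; the SD of 20 is the one implied by 35 per arm. The patient-reported primary outcome does not depend on the raters and is unaffected. This should be fixed before rating starts, but it does not threaten the trial's main comparison.

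**What to change.** 1. Base the analysed OPTION5 score on the second researcher and the patient representatives, provided that none of them has a role in enrolment, randomisation or data entry. The article does not say this of the second researcher, so it must be confirmed.
2. Use the principal investigator's scores only for inter-rater reliability or a sensitivity analysis, and keep that person out of discrepancy resolution, whether by agreement or by a fifth rating.
3. Give the raters whose scores are analysed ID-coded recordings in random order, without access to allocation data, and have them record a guess of the arm for each recording. This restriction is for those raters only; the principal investigator needs REDCap for the duties described.
4. Replace the blinding sentence with wording such as: raters of the analysed score are not told the allocation; audio content may reveal it.

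**Cost.** Recruitment, sample size and data collection do not change. There is some loss of reliability. As an indication, take the article's ICC threshold of 0.6 as the reliability of a single rating and treat raters as interchangeable (both assumptions). By Spearman-Brown, the mean of three ratings has reliability 3 × 0.6 / (1 + 2 × 0.6) = 0.82, and the mean of two has 2 × 0.6 / (1 + 0.6) = 0.75. A patient representative would also supply one of the two analysed ratings on each recording, although part of the purpose of involving them is to find elements that the researchers miss. The joint calibration session therefore carries more weight.
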